#### Clinical phase

2.9.3

The clinical phases consist of 3 stages which prolong 20 minutes each (60 minutes total). The first and third stages are stable state. The second stage is to practice resource or stress mindfulness meditation. Before the clinical trial, at first stage, subjects will fill in the Pre clinic Phase (=Mibyung) Questionnaire, psychosocial wellbeing index short form,^[21]^ hospital anxiety and depression scale,^[22]^ Korean sex role inventory-short form,^[23]^ five facet mindfulness questionnaire short scale,^[24]^ the Korean version of positive affect negative affect schedule,^[25]^ the core seven emotions inventory-short form,^[26]^ and Korea Sasang Constitutional Diagnostic Questionnaire-15.^[27]^

At 1 and 3 stages, qEEG measurements were taken through 10 minutes (5 minutes with eyes open and 5 minutes with closed eyes) from 5 minutes after the beginning of the stage. In the second stage, the qEEG measurements were taken for 20 minutes with eyes closed. During 1, 2, and 3 stages, the 24-hour Holter monitoring was measured and HRV evaluated at each stage. The blood pressure and pulse were measured before and after the second stage.

After the clinical trial, at third stage, subjects filled the Five Facet Mindfulness Questionnaire Short Scale (FFMQ-S),^[24]^ the Korean version of positive affect negative affect schedule (K-PANAS),^[25]^ the core seven emotions inventory-short form (CSEI-SF),^[26]^ and confirmation abnormal reaction.

#### Clinical trial phases: mindfulness meditation

2.9.4

Mindfulness is awareness training that observes what is happening in this moment as it is.^[28,29]^ It is a method to increase inner strength by examining the uncritical and nonjudging aspects of thoughts that arise from “deep inside,” while remaining at the bottom of consciousness. The resource or stress mindfulness guideline script will follow the M&L Psychotherapy Manual,^[30]^ and the Meditation Guide will be directed by trained mentors trained by the M&L Psychotherapist course. It should be noted that the drug injections or physician treatment that affect EEG and heart during clinical trials are prohibited.

#### Test group intervention: resource mindfulness group

2.9.5

Resource mindfulness is to experience a safe and comfortable state by recalling the positive nourishment (resource) inside subject within the mindfulness state

#### Active comparator group intervention: stress mindfulness group

2.9.6

Stress mindfulness is to experience emotions, feelings, memories, thoughts, and so on occurring within me when I recall a difficult situation inducing stress in the state of mindfulness.

### Outcome measures: primary outcomes and measures

2.10

#### qEEG

2.10.1

The EEG of the subjects will be measured in a comfortable, quiet, cool room, wearing an electro-cap (Electro-cap; Mitsar, Russia) with 21 surface electrodes placed in an international 10/20 system, for 5 minutes each in open-eye and closed-eye states. All electrode impedance will be less than 5 KΩ, based on the method of Ferree et al.^[31]^ The reference electrode will be located between Fz and Cz; the amplifier will be a Mitsar-EEG 201 machine (Mitsar, Russia). Artifacts of the recorded EEG, modified automatically, will be manually removed by the qEEG expert for a reliability measurement of 0.9 or better. Spectral analysis, coherence, and Low Resolution Brain Electromagnetic Tomography analysis will be performed with WinEEG for records with artifact-free EEG segments >2 minutes and split-half reliability >95%. Spectral analysis will use linked-ears reference montage and local average (Laplacian) montage.^[32,33]^ Linked-ears reference montage will be used as a general criterion; local average (Laplacian) montage can emphasize localized areas and minimize the overall effect of drugs on the brain.^[34]^ The absolute power and relative power will be calculated as delta (0.5–4 Hz), theta (4–8 Hz), alpha (8–12 Hz), and beta (12–20 Hz), respectively, using the absolute power and relative power. Neuro-guide will be used as the basis for all analyses; EEG analysis will be conducted by BCN, an expert KMD. In addition, the EEG results will be analyzed by KMD and CP after mentoring by a neuro feedback supervisor (BCN) and biofeedback specialist on Applied Psychophysiology in the United States.

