**Methods::**

This randomized, controlled, assessor-blinded, 2-armed, parallel, multicenter clinical trial will analyze a total of 50 subjects, including 25 each for the test group and the active control group. Subjects will be randomly allocated to the test group (performing resource mindfulness) and the control group (performing stress mindfulness) in a 1:1 ratio. The clinical trial consists of 3 stages. The first and third stages are stable states. The second stage is divided into the test and active comparator groups. Quantitative EEG (qEEG) measurements at stages 1 and 3 will be recorded for 10 minutes; measurements at stage 2 will be recorded for 20 minutes with the eyes closed. The 24-hour Holter Monitoring and heart rate variability will be evaluated at each stage. Before the beginning of stage 3, subjects will complete the questionnaires. The primary outcome will be analyzed by independent *t* tests of both groups.

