### Trial design and study setting

2.2

This clinical research will be conducted with subjects who provide voluntary consent and will be reviewed according to the inclusion or exclusion criteria of the clinical trial plan. Selected subjects will be assigned randomly into the test or active comparator group, according to precompleted random templates. The study design is as follows. This randomized, controlled, single-blinded, 2-armed, parallel, clinical trial will collect a total of 50 subjects, including 25 each for the test and active comparator groups. The subjects will be randomly allocated to a test group performing resource mindfulness (RM), and a control group performing stress mindfulness (SM), at a 1:1 ratio. The clinical trial consists of 3 stages, 20 minutes each (60 minutes total). The first and third stages are stable states. The second stage is divided into the test group and the active comparator group. The test group subjects will practice RM meditation and the active comparator group subjects will practice SM meditation. RM or SM meditation guide scripts will follow the M&L Psychotherapy Manual and the meditation guide will be directed by a professional practitioner trained by the M&L psychotherapist course. At stages 1 and 3, qEEG measurements will be taken for 10 minutes (5 minutes with eyes open and 5 minutes with eyes closed) from 5 minutes after the beginning of the stage. In the second stage, the qEEG measurements will be taken for 20 minutes, with eyes closed. The 24-hour Holter monitoring^[20]^ will be performed through stages 1, 2, and 3; HRV will be evaluated during each stage. The blood pressure and pulse will be measured before and after the second stage. All processes related with clinical trial including plans for collecting, assessing, reporting, and managing solicited and spontaneously reported adverse events and other unintended effects of trial interventions or trial conduct will be monitored and modified primarily by researcher director and peer researchers to ensure participants’ safety and research design's accuracy. A diagram and the time schedule of this study are shown in Table 1 and Fig. 1.

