#### 24-Hour Holter monitoring

2.10.2

Heart rate variability is most commonly used to observe changes in the autonomic nervous system response.^[15]^ This allows quantitative measurement of the activity of the autonomic nervous system, is easily applicable, and is noninvasive to the subjects. In addition, it can continuously monitor the electrical activity of the heart to understand the inter-relationship of rhythm disorders, such as dizziness, chest pain, syncope, palpitations, and tachycardia, and to evaluate the mechanisms of arrhythmia, abnormal blood dynamics, and rhythm disorders. Therefore, in clinical practice, 24-hour Holter monitoring is a widely used method.^[35]^ The spectral density value (power spectral density, msec^2^) is calculated for the low-frequency component (0.04–0.15 Hz) and the high-frequency component (0.15–0.4 Hz) in frequency domain analysis (spectrum analysis). Then, the low-to-high frequency ratio (LF/HF) of the low-frequency spectrum is analyzed; it is compared with mean NN (mean of all coupling intervals between normal beats), SDNN (standard deviation of all normal RR intervals over 10 minutes), pNN50 (percent of differences between adjacent normal RR intervals of >50 ms during 10 minutes), and rMSSD (square root of the mean squared differences of successive NN intervals) in the time-domain analysis. Low-frequency domain values among indicators in the frequency domain represent the activity of the sympathetic nervous system. High-frequency domain values represent the activity of parasympathetic nerves. SDNN, rMSSD, and pNN50 are indicators of time domain that are used as indicators of the vagus nerve dominance pattern in the heart. In addition, active blood pressure monitoring can observe changes in blood pressure by simultaneously observing systolic and diastolic blood pressures before and after intervention, such as meditation. Biochemical markers such as insulin, fasting blood glucose and lipid levels, and changes in insulin resistance and blood lipid levels can be used to assess the associations of cardiovascular risk factors with biomarkers.^[36]^ The measurement and flow chart is Fig. 2.

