### Sample size calculation

2.13

Based on the clinical trial study, the number of subjects was calculated as a minimum of 25 subjects each in the test and control groups, considering a 10% dropout rate. Based on previous studies,^[37,38]^ using the G∗power program, the total effect size was set at 1.0, and the total number of samples in the 90% confidence interval (CI) was set at 46 subjects. Considering a dropout rate of 10%, 50 participants must be recruited to collect sufficient data for statistical analysis and interpretation.

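### The trial is sized for one comparison, but section 2.10 places the whole qEEG and HRV output under the primary heading without fixing a variable

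*Protocol article*

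**What the plan says.** The abstract (Methods) uses the singular: "The primary outcome will be analyzed by independent" t tests of the two groups. It does not name the variable.

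Section 2.13 sizes the trial on a single standardised effect, also tied to no variable: "the total effect size was set at 1.0", and "the total number of samples in the 90% confidence interval (CI) was set at 46 subjects". It then adds a dropout allowance: "Considering a dropout rate of 10%, 50 participants must be recruited". Section 2.2 confirms equal arms, "including 25 each for the test and active comparator groups".

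Section 2.10 is headed "Outcome measures: primary outcomes and measures". Three subsections sit under it:

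- **2.10.1, qEEG.** 21 electrodes, four frequency bands, absolute and relative power, two montages (linked-ears being the default), eyes open and eyes closed. Also: "Spectral analysis, coherence, and Low Resolution Brain Electromagnetic Tomography analysis will be performed with WinEEG".
- **2.10.2, Holter.** LF and HF power, then: "Then, the low-to-high frequency ratio (LF/HF) of the low-frequency spectrum is analyzed", with mean NN, SDNN, pNN50 and rMSSD alongside. Section 2.2 has HRV evaluated in each of the three stages.
- **2.10.3, questionnaires.**

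There is no secondary-outcome heading. Section 2.14 compares the groups instrument by instrument (qEEG, Holter, three questionnaires) and singles out no variable within any of them.

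**The concern.** The abstract and the sample size presuppose one primary comparison, while the outcome section presents whole measurement domains as primary. Both cannot describe the same plan. Until one variable is fixed, d = 1.0 cannot be judged for plausibility, because nobody can say what it is a standardised difference of.

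The choice of primary result also stays open until the data are in. Any band, site, eye state, stage or HRV index that reached p < 0.05 could be reported as the primary finding without departing from the text. A positive result would then not carry the 5% error rate that readers attach to a primary test.

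**Working it through.** **1. Reproducing the stated sample size.** Inputs: d = 1.0, 1:1 allocation, total 46 (sections 2.2 and 2.13). Alpha and power are not stated. I assume two-sided 0.05 and read the 90% figure as power.

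- Normal approximation: n per arm = 2 × (1.960 + 1.282)² / 1.0² = 21.02, so 22 per arm and 44 in total.
- Noncentral t: n per arm = 22.02, so 23 per arm and 46 in total, an exact match. Power is just under 90% at 22 per arm (0.8997) and 91.2% at 23.
- Two-sided 0.10 (or one-sided 0.05) with 95% power also gives 46. The inputs therefore do not identify one calculation, but each of these readings is a single unadjusted comparison.

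**2. What the primary heading contains.** I count only what section 2.10 specifies, and only in the default linked-ears montage.

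- Spectral power per recording: 21 electrodes × 4 bands × 2 power types = 168. If two of the 21 are ear references (assumption), 19 × 4 × 2 = 152.
- HRV per stage: LF, HF, LF/HF, mean NN, SDNN, pNN50, rMSSD = 7.
- Smallest combined set, one recording and one stage: 152 + 7 = 159.

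Coherence, LORETA, the Laplacian montage, and further stages and eye states are left out. They could only add to the count.

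**3. Error rate if every value in the set were tested at 0.05 with no true differences.**

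Under independence, the chance of at least one false positive is 1 − 0.95^m:

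- m = 7: 1 − 0.95^7 = 30%
- m = 159: 1 − 0.95^159 = 99.97%

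The expected number of false positives does not depend on correlation: 159 × 0.05 = 8.0.

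qEEG channels are correlated, so I simulated null outcomes with 23 per arm and 1,500 replicates per setting. With the same correlation between all outcomes:

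| Correlation | 7 tests | 159 tests |
|---|---|---|
| 0 | 31% | 99.9% |
| 0.3 | 29% | 99% |
| 0.5 | 24% | 88% |
| 0.7 | 16% | 58% |
| 0.9 | 10% | 24% |

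A second setting used eight band-by-power-type blocks of 19 electrodes. Correlation was 0.8 to 0.95 within blocks and 0.2 to 0.6 between them. The seven HRV indices were correlated 0.6 with each other and independent of the EEG. The 159 tests then gave 57% to 88%.

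**4. Power under the remedies**, at d = 1.0 and 23 per arm:

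- One primary variable at 0.05: 91%.
- Two with Holm: each has at least its power at 0.025, which is 85%. If both effects are 1.0 and independent, each has about 0.854 + (0.912 − 0.854) × 0.854 = 0.904.
- All seven HRV indices for one stage kept primary with Bonferroni: 71%; 90% power would need 68 evaluable subjects.

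**The case against.** A reader might infer that the protocol lists hundreds of primary variables, gives each an unadjusted test, and so makes a chance finding almost certain. The document does not support that.

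- It lists no such set. Section 2.10.1 mostly describes acquisition and processing, and the counts above come from multiplying its factors. The heading also covers the questionnaires, so it may simply be loose.
- Section 2.14 does not say that every electrode and band is tested, states no alpha, and says nothing for or against adjustment. A multiplicity rule could stand in an analysis plan or in the full protocol (version 2.3), neither of which is shown. Its absence from the article is not a finding.
- Near-certainty requires weak correlation. Neighbouring electrodes, and absolute and relative power from one recording, are plausibly strongly correlated. At a common correlation of 0.9 the rate for 159 tests is 24%.
- Counting both montages equally would inflate the total, since the protocol makes linked-ears the default. That is why only linked-ears is counted here.

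All of this stands, and it limits how strongly the point can be put. It does not answer the core. The article addresses primary outcomes under its own heading and leaves the variable open, against its own singular wording and single-comparison sample size. An adjustment rule elsewhere would not say which variable the 46 subjects were calculated for.

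**Conclusion.** The concern holds in this form: the trial is sized for one comparison and announces one primary outcome, but the primary heading covers entire qEEG and HRV domains with no variable fixed. This should be corrected, because the primary inference is undefined.

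The error-rate figures are conditional on testing the whole set at 0.05 with no true differences. On that condition:

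- the seven HRV indices alone give about 30% if independent, and about 10% at a common correlation of 0.9;
- one linked-ears recording plus the HRV indices gives roughly 24% to nearly 100%, depending on correlation.

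Every scenario examined is well above 5%, but not every one is close to certainty. The match to 46 rests on reading the calculation as two-sided 5% with 90% power.

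**What to change.** Before any outcome data are examined, name one primary variable from those already recorded. State the measure, band or index, site or average over sites, montage, eye state and stage contrast (those that apply). The stated 46 then remains valid, provided d = 1.0 is defensible for that variable. The choice is the investigators'.

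Alternatively, name two primary variables, for example one qEEG and one HRV, and test them with Holm at an overall two-sided 5%. Call them two primary outcomes rather than co-primary, since the latter commonly means that both must succeed.

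In either case, label all other qEEG, HRV and questionnaire comparisons secondary or exploratory.

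The cost is a wording change in section 2.10, with sections 2.13 and 2.14 brought into line, and an update of the registration where needed. No new measurement is required. One primary variable costs no power. With two, the downside is that guaranteed power for each falls from 91% to about 85% at 23 per arm; 90% at the 0.025 level would need 54 evaluable subjects. Recruitment has already begun (section 3.1), so this should be done promptly.

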#### 24-Hour Holter monitoring

2.10.2

Heart rate variability is most commonly used to observe changes in the autonomic nervous system response.^[15]^ This allows quantitative measurement of the activity of the autonomic nervous system, is easily applicable, and is noninvasive to the subjects. In addition, it can continuously monitor the electrical activity of the heart to understand the inter-relationship of rhythm disorders, such as dizziness, chest pain, syncope, palpitations, and tachycardia, and to evaluate the mechanisms of arrhythmia, abnormal blood dynamics, and rhythm disorders. Therefore, in clinical practice, 24-hour Holter monitoring is a widely used method.^[35]^ The spectral density value (power spectral density, msec^2^) is calculated for the low-frequency component (0.04–0.15 Hz) and the high-frequency component (0.15–0.4 Hz) in frequency domain analysis (spectrum analysis). Then, the low-to-high frequency ratio (LF/HF) of the low-frequency spectrum is analyzed; it is compared with mean NN (mean of all coupling intervals between normal beats), SDNN (standard deviation of all normal RR intervals over 10 minutes), pNN50 (percent of differences between adjacent normal RR intervals of >50 ms during 10 minutes), and rMSSD (square root of the mean squared differences of successive NN intervals) in the time-domain analysis. Low-frequency domain values among indicators in the frequency domain represent the activity of the sympathetic nervous system. High-frequency domain values represent the activity of parasympathetic nerves. SDNN, rMSSD, and pNN50 are indicators of time domain that are used as indicators of the vagus nerve dominance pattern in the heart. In addition, active blood pressure monitoring can observe changes in blood pressure by simultaneously observing systolic and diastolic blood pressures before and after intervention, such as meditation. Biochemical markers such as insulin, fasting blood glucose and lipid levels, and changes in insulin resistance and blood lipid levels can be used to assess the associations of cardiovascular risk factors with biomarkers.^[36]^ The measurement and flow chart is Fig. 2.

**Figure 2 F2:**
[figure not shown]
Flow chart of clinical trial design (qEEG and 24-hour Holter monitor). qEEG = quantitative electroencephalogram.

#### Others

2.10.3

Before the clinical trial, the subjects will complete questionnaires such as the constitutional diagnosis questionnaire, Korea Sasang Constitutional Diagnostic Questionnaire-15 (KS-15),^[27]^ hospital anxiety and depression scale (HADS),^[22]^ psychosocial wellbeing index short form (PWI-SF),^[21]^ KSRI-F,^[23]^ FFMQ-S,^[24]^ K-PANAS,^[25]^ and CSEI-SF.^[26]^ For the clinical trial, within 10 minutes before the start of phase 3, the subjects will complete the FFMQ-S,^[23]^ K-PANAS,^[24]^ and CSEI-SF^[25]^ questionnaires, and Confirmation abnormal reaction.

### Safety assessment

2.11

Physical examinations will be performed, and vital signs and adverse events will be checked at every visit. To examine the safety of meditation, the KS-15,^[27]^ chest radiograph, electrocardiogram, clinical pathology ([hematology: hemoglobin, hematocrit, red blood cell count, white blood cell count, platelet count, white blood cell percentage], blood chemistry, gamma-glutamyl transpeptidase, alkaline phosphatase, blood urea nitrogen, creatinine, T-bilirubin, and glucose], pregnancy test (urine HCG test), and infectious disease test by KMD and CP at the screening visit will be conducted by KMD or CP. physicians with ≥5 years of clinical experience will oversee the clinical evaluations.

During the clinical trial, any adverse event will be recorded and assessed in case report form (CRF). It will be calculated to the adverse event occurrence ratio. Adverse events associated with the meditation intervention will be monitored and appropriately handled by KMD and CP.

### Data management and quality control

2.12

The CRC will collect data on a paper CRF. Records including medical records, questionnaires, consent forms, and other clinical trial relevant papers will be stored at each site in a locked cabinet or a password-protected computer that can be accessed only by an authorized individual and kept confidential, even when the results of the clinical trial are published. However, quester, monitor, and inspectors related to this clinical trial can view each subject's records for the purpose of monitoring and checking this clinical trial and management of the subject's progress. Additionally, all documents related to this clinical trial, such as case histories, will be recorded and distinguished by using each subject's identification code (typically the subject's initials), but not by using any subject's name. After completion of the outcome report, the research will be kept for 5 years from the end of the clinical trial.

### Sample size calculation

2.13

Based on the clinical trial study, the number of subjects was calculated as a minimum of 25 subjects each in the test and control groups, considering a 10% dropout rate. Based on previous studies,^[37,38]^ using the G∗power program, the total effect size was set at 1.0, and the total number of samples in the 90% confidence interval (CI) was set at 46 subjects. Considering a dropout rate of 10%, 50 participants must be recruited to collect sufficient data for statistical analysis and interpretation.

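### The sample size of 46 is justified by a 90% confidence interval, which is not an input to a two-group calculation, and 50 recruits less 10% leaves 45, not 46

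*Protocol article*

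**What the plan says.** The sample-size section (2.13) names G*Power and gives four figures.

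- Effect size: "the total effect size was set at 1.0". The type of effect size is not named.
- Basis and result: "the total number of samples in the 90% confidence interval (CI) was set at 46 subjects".
- Recruitment: "Considering a dropout rate of 10%, 50 participants must be recruited".
- Per arm: "a minimum of 25 subjects each in the test and control groups, considering a 10% dropout rate".

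The article states no alpha, sidedness or power. The abstract's Methods paragraph names the primary test, "The primary outcome will be analyzed by independent *t* tests of both groups", and says that the trial "will analyze a total of 50 subjects".

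**The concern.** Two statements in section 2.13 do not work as written.

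First, a confidence level and an effect size do not determine a sample size for comparing two groups. The 90% may be the power under another name, or it may be one minus alpha. The first reading goes with a conventional 5% error rate, the second with 10%. Because the article did give a basis for the number, this is a misstated parameter and not a detail left to a fuller document.

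Second, the section gives a required number (46), a dropout rate (10%) and a recruitment target (50), and the three do not fit together. The abstract adds to this by describing 50 as the number analysed, where section 2.13 makes it the number recruited to allow for losses.

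At stake is whether a reader can tell which error rate and power the trial was sized for, and whether the target delivers the number the protocol itself requires.

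**Working it through.** **Inputs.** From section 2.13: effect size 1.0, total 46 (23 per arm), dropout 10%, 50 recruits (25 per arm). From the abstract: independent t test, 1:1 allocation. Assumption: 1.0 is Cohen's d for the difference between the two arms.

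**Method.** Power of the two-sample t test from the noncentral t distribution, as G*Power computes it:

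- df = n1 + n2 − 2
- noncentrality = d × √(n1·n2/(n1 + n2))
- power = probability that the noncentral t exceeds the critical value (both tails if two-sided)

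**Step 1: reproduce 46.** With 23 per arm, df = 44 and noncentrality = √(23 × 23/46) = √11.5 = 3.391. With 22 per arm, df = 42 and noncentrality = √11 = 3.317.

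| Setting | Power target | Power at 22 per arm | Power at 23 per arm | Smallest total |
|---|---|---|---|---|
| two-sided alpha 0.05 | 90% | 89.97% | 91.2% | 46 |
| two-sided alpha 0.10 | 95% | 94.7% | 95.5% | 46 |
| one-sided alpha 0.05 | 95% | 94.7% | 95.5% | 46 |

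All three settings give exactly 46, so the number itself is sound but does not identify the setting. Taking the 90% interval as two-sided alpha 0.10 gives 46 only with a 95% power target. At that alpha, 80% power needs 28 in total and 90% power needs 36.

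**Step 2: dropout.**

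- Evaluable from 50 at 10% loss: 50 × 0.90 = 45, one below 46.
- Recruits needed for 46 evaluable: 46/(1 − 0.10) = 51.1, so 52 at 1:1 (26 per arm).
- The cruder inflation, 46 × 1.10 = 50.6, gives 51. Neither method gives 50.
- Loss that 50 recruits can bear: (50 − 46)/50 = 4/50 = 8%.

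**Step 3: what one fewer participant costs.** With 22 and 23 evaluable, df = 43 and noncentrality = √(22 × 23/45) = 3.353.

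| Setting | Power with 45 evaluable | Power with 46 evaluable |
|---|---|---|
| two-sided alpha 0.05 | 90.6% | 91.2% |
| two-sided alpha 0.10 | 95.1% | 95.5% |
| one-sided alpha 0.05 | 95.1% | 95.5% |

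Each setting still meets its own target. If all five losses fell in one arm (20 and 25, noncentrality √(500/45) = 3.333), power at two-sided 0.05 would be 90.3%.

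**The case against.** The best defence is that little depends on this. The figure 46 reproduces exactly. The simplest explanation is that 90% is power, mislabelled, alongside a conventional two-sided 5% level. The dropout slip is one participant and leaves power above target. The discussion says that measurement and intervention take place in one day, so there is little follow-up in which to lose anyone. Section 2.13 also calls 25 per arm a minimum. A condensed article may leave alpha and sidedness to the full protocol or the analysis plan. The abstract's 50 could simply mean that everyone randomised is analysed.

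Most of this stands, and it limits the severity. It does not rescue the wording: the stated basis is the wrong kind of quantity, and 46, 10% and 50 cannot all be right. The mislabelled-power reading is plausible, but the other two settings fit equally well.

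A reader might infer three stronger points, which the article does not support.

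- *The trial will declare success at p < 0.10.* Section 2.13 is about sample size. Neither it nor the statistical section (2.14) sets a decision threshold. Ambiguity about alpha is not a plan to test at 10%.
- *The calculation is for a t test while the analysis uses rank tests.* The Wilcoxon tests in section 2.14 compare with baseline. The between-group step there names no test, and the abstract names independent t tests for the primary outcome. A t-test calculation matches that, and power figures for a rank-sum test would describe an analysis that nobody planned.
- *Alpha was 0.05 two-sided.* This is the conventional choice and it fits, but the text does not establish it.

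**Conclusion.** The point holds as a misstatement with small consequences. The basis given for 46 is not a sample-size input, and three different combinations of alpha, sidedness and power yield the same number, so the intended error rate cannot be read from the article. The recruitment target is one evaluable participant short of the protocol's own requirement at its own dropout rate. It would cover 8% loss, or else the target would have to be 52.

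Power falls by about half a percentage point and stays above target: 90.6% at two-sided 0.05 and 95.1% at two-sided 0.10 with 45 evaluable. The abstract's 50 analysed is loose wording that matches section 2.13 only if no one is lost to the analysis.

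All of this assumes that effect size 1.0 is Cohen's d and that the t test in the abstract is the primary comparison. Severity: minor to should-fix. Nothing here shows that the trial is underpowered at the assumed effect or that more participants are needed.

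**What to change.** Three changes of wording, with no change to enrolment:

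1. In section 2.13, replace the confidence-interval phrase with the alpha, sidedness and power actually entered in G*Power, confirmed by the sponsor from its own record, and name the effect size as Cohen's d if that is what it was. If the record shows two-sided 0.05 and 90% power, the sentence can read: independent t test, d = 1.0, two-sided alpha 0.05, 90% power, 23 per arm, 46 in total.
2. Reconcile the dropout statement. Either say that 50 recruits allow 8% dropout, or keep 10% and say that 45 would then be evaluable, with the power recomputed for the confirmed alpha (90.6% at two-sided 0.05; 95.1% at two-sided 0.10 or one-sided 0.05).
3. In the abstract, describe 50 as the number recruited, or state that all 50 randomised will be analysed if that is meant.

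The cost is a look-up of the G*Power settings and a few edited sentences. The article reports that recruitment is already under way, so the settings should be put on record before the data are analysed.
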